### Study design and population

We will use a cluster-randomized trial study designed with both intervention and control arms. The study will involve 268 children (134 controls and 134 patients who receive intervention) aged 2–14 years who are attending CTC and who have a viral load of >1000 copies/ml.

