### Recruitment

The healthcare workers (i.e. ART nurses) will identify and recruit children with a viral load of >1000 copies/ml and who were aged 2–14 years. Before recruitment, informed consent will be obtained from their caregivers.

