### Outcome measures

The study will have two outcome measures. The primary measure will be the adherence, this will be measured by using the standard adherence tool (National AIDS Control Program [32]) and loss to follow-up (retention in CTC), which will be compared in both arms. We will measure these metrics at baseline, subsequent follow-up, and the study’s end (i.e. 6 months). The secondary measure will be the viral load, which will be measured at the baseline and subsequently at the 6-month study’s end, comparing both arms.

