### Measurement of variables

#### Dependent variable

The dependent variable will be the viral load cell count and it will be classified as suppression when the count is <1000 copies/ml and unsuppressed when >1000 copies/ml.

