#### Independent variable

The independent variables will be age, weight, adherence, and opportunistic infection (i.e. TB). The caregivers’ social demographic characteristics, age, sex, level of education, income, and marital status will be the independent variables.

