### Data processing and analysis

We will enter data into Excel™ software and analyze it using Stata™ software. Descriptive statistics will summarize continuous data, such as the mean, median, standard deviation, and interquartile range. We will use frequencies and percentages to summarize categorical data. Multiple statistical tests and methods will be employed. The univariate analysis will typically utilize Pearson’s chi-squared correlation or Fisher’s exact test, where appropriate. As for the primary outcome (mean difference in the viral load of HIV-positive children with VLS), we will use an independent *t*-test to compare the means of participants in the intervention and control arms. We will develop a multivariable regression model, adjusting for clustering and other confounders for potential confounding. We will use proportions and tests for different proportions as measures of improvement using the difference in difference. All statistical tests will be two-sided and *P* < 0.05 will be considered statistically significant.

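### If the difference in difference is meant for viral suppression it is redundant, because eligibility sets baseline suppression at 0% in both arms; the collected baseline viral load is not a listed covariate

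*Protocol article*

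**What the plan says.** - Study design and population restricts the trial to children "aged 2–14 years who are attending CTC and who have a viral load of >1000 copies/ml". Recruitment repeats this: ART nurses "will identify and recruit children with a viral load of >1000 copies/ml".
- Dependent variable sets the outcome at the same cut-off: "it will be classified as suppression when the count is <1000 copies/ml and unsuppressed when >1000 copies/ml".
- Data processing and analysis then states: "We will use proportions and tests for different proportions as measures of improvement using the difference in difference". The sentence names neither the outcome nor a model. The same section separately plans a t-test comparing mean viral load between arms, and a multivariable regression that allows for clustering and confounders, with no link function or time interaction stated.
- Outcome measures confirms that a baseline value will exist: "The secondary measure will be the viral load, which will be measured at the baseline and subsequently at the 6-month study’s end". Baseline data also lists suppression status among the items collected.
- Independent variable begins: "The independent variables will be age, weight, adherence, and opportunistic infection (i.e. TB", and goes on to the caregivers' characteristics. Baseline viral load is not among them.

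**The concern.** A difference in difference is useful when arms may differ at baseline on the outcome and that difference should be removed. Here the entry criterion and the outcome definition share one cut-off, so for suppression there is no baseline difference to remove. A reader who sees the method named may believe that the analysis corrects for baseline status, when it uses no baseline information at all.

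The baseline information that does vary between children is how far above 1000 copies/ml each one starts. This is likely to be prognostic for reaching suppression by 6 months and it is already collected, yet the listed covariates leave it out. What is at stake is modest: clarity about the analysis of suppression, and some precision that costs nothing to obtain.

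**Working it through.** **Inputs.** Baseline suppression is 0 in both arms (Study design and population, Recruitment, Dependent variable). There are 134 children per arm, with assumed suppression of 18% and 30% (Sample size calculation and selection). In whole children, 18% and 30% of 134 are about 24 and 40.

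**Step 1: plain 6-month comparison.**
- Control: 24/134 = 0.1791. Intervention: 40/134 = 0.2985.
- Difference: 16/134 = 0.1194.
- SE = √[(0.1791 × 0.8209 + 0.2985 × 0.7015)/134] = √(0.3564/134) = 0.0516.

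**Step 2: difference in difference on the risk scale.**
- (40/134 − 0/134) − (24/134 − 0/134) = 0.1194.
- The baseline terms are constants, so they add no variance and the SE is again 0.0516. A fitted linear arm-by-time model, with standard errors clustered by child, gives 0.1194 (SE 0.052).
- Clinic clustering was left out of this example. It does not break the identity at clinic level: baseline suppression is zero in every clinic, so each clinic's change equals its 6-month proportion.

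**Step 3: what would happen in logistic form.**
- With no events in either baseline cell, an arm-by-time logistic model has no finite maximum-likelihood solution. As the iteration limit was raised from 10 to 25 to 35, the intercept drifted from about −11 to −22 to −25, and the SE of the interaction rose from 33 to 12,706 to 101,338.
- The 6-month-only logistic model is stable: log odds ratio = ln[(40 × 110)/(24 × 94)] = 0.668, SE = √(1/40 + 1/94 + 1/24 + 1/110) = 0.294, p = 0.023.

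**Step 4: what baseline viral load could add.** For log10 viral load as a continuous outcome, with equal variance at both times and correlation r, adjusting for baseline multiplies the variance of the unadjusted 6-month comparison by 1 − r². The protocol gives no r, so an illustrative range is assumed:

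| r | 1 − r² | variance saved |
|---|---|---|
| 0.2 | 0.96 | 4% |
| 0.3 | 0.91 | 9% |
| 0.4 | 0.84 | 16% |
| 0.5 | 0.75 | 25% |

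These factors concern the variation between children, and they do not carry over directly to the binary outcome.

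**The case against.** Several objections carry weight.

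- **No harm on the stated scale.** The sentence speaks of proportions, and on that scale the estimate and its SE are the same either way. This stands: the method is redundant and would not mislead numerically.
- **The sentence may not concern suppression.** Adherence is also an outcome measured at baseline, and eligibility does not fix it, so a difference in difference on adherence would not be empty. The Abstract describes the suppression analysis as a between-arm comparison of proportions without mentioning difference in difference. Yet it speaks of improvement right after naming suppression, so the suppression reading is plausible but not the only one. This stands, and is why the point is conditional.
- **Exactly 0% is the design intention, not a certainty.** The protocol does not say whether the result used for eligibility is also the baseline result. If viral load were measured anew, a few children could be below 1000 copies/ml. Even then, randomisation makes the direct 6-month comparison valid without subtracting a chance imbalance.
- **The covariate list may not be final.** It appears under measurement of variables, and the analysis section refers only to other confounders. This stands: baseline viral load is unlisted, which is not the same as excluded.

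Three stronger readings are tempting and should be resisted. A reader might infer that the planned analysis cannot be estimated, but that needs a logistic arm-by-time model, and none is named. A reader might infer that difference in difference takes the place of baseline adjustment, but a separate adjusted regression is planned and nothing links the two. A reader might also infer an inefficient change-score analysis of viral load, but none is stated; the comparison given is a t-test of means.

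**Conclusion.** The point holds as a limited one. Provided the eligibility result serves as the baseline value, suppression at baseline is 0% in both arms, and a difference in difference on suppression is the 6-month difference under another name: 0.119 by either route at the planned rates. It introduces no bias and loses no precision, and whether it applies to suppression at all is unclear from the text. The failure in logistic form is a hazard to avoid, not a defect of a stated model.

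The practical gain lies in the covariate. Baseline viral load will be in hand and is not listed. For the continuous outcome, the variance saving would be 4% to 25% if the correlation lay between 0.2 and 0.5, a range that is assumed. This is an inexpensive improvement and not a threat to the trial's validity.

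**What to change.** - State which outcome the difference in difference is for, and drop it for suppression.
- For suppression, compare the proportion below 1000 copies/ml at 6 months directly between arms in the cluster-adjusted regression already planned, with baseline log10 viral load as a covariate. Name the effect measure, because adjusting for a prognostic covariate changes what an odds ratio estimates.
- If viral load is also analysed as a continuous outcome, replace the unadjusted t-test with 6-month log10 viral load adjusted for baseline log10 viral load in the same clustered model.
- Add baseline viral load to the listed independent variables, and say whether the eligibility result and the baseline result are the same test.

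The cost is a few sentences in the analysis and variables sections and one more child-level covariate in the model. No new data, visits or participants are needed.

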### Dissemination of results

We will present the findings from this study to the Simiyu Regional Health Management Team. We will also present this study at the President’s Office, Regional Administrative Secretary, and Local Government’s (PO-RALG) Directorate of Health, Nutrition, and Social Welfare. We will present the finding at local and international conferences and publish the study in an international peer-reviewed journal.

### Ethical clearance and consent to participate

In the first stage, we will obtain the ethical clearance and registration for this study from the Dodoma University Ethical Board. In the second stage, we will require permission to use the CTC2 database from the Ministry of Health. We will seek consent from other authorities in the third phase including the PO-RALG. In the fourth stage, we will seek permission from the person in-charge of health facilities. In the last step, we will seek approval and written consent from participants. Our study was registered in the Pan African Clinical Trial Registry with a registration number PACTR202111867711522.

## Discussion

This Konga model study will be the first cluster-randomized clinical control trial study in Tanzania using the community as a basis for addressing challenges in VLS. The existing community of PLHIV will enhance ART adherence with VLS in children.

A systematic review of community-based interventions highlighted the importance of carefully designing organization-based HIV prevention interventions in a way that would improve their effectiveness and efficiency [33]. The current study will use community participation to promote retention and adherence to treatment, focusing on home-based follow-up and psychosocial and peer support [29]. Several studies have demonstrated that poor adherence and retention in ART care detract from VLS among children [34–37] living with HIV. In this intervention, we will use the Kong to promote retention and adherence to ART among children receiving ART to reduce their viral loads.

Opportunistic infections, such as TB, have been shown to hamper VLS in children receiving ART [14, 19, 20, 38]. Another study demonstrated that the initiation of ART in children reduces the incidence of TB [24]. The Konga model will include active home visits to screen children for TB and other co-morbidities in the control arm. The screening will help to identify early infection [24] and facilitate referral to the treatment point.

HIV-infected children potentially suffer from mental-health disorders that result in poor quality of life, HIV disease progression; poor compliance and increased mortality [39]. Studies have demonstrated that psychiatric morbidity in HIV-infected children is higher than that in children in the general population. These studies recommended that there is a need to incorporate psychiatric liaison service routine care for HIV-infected children [40–42]. The personnel from the Konga will visit the children and their families to provide psychosocial counseling and support.

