## Abstract

This study aims to test the effectiveness of a community-based intervention (Konga model) to improve viral-load suppression in children living with human immunodeficiency virus (HIV) and enrolled in care and treatment centers in Tanzania mainland. The study will be a cluster-randomized clinical trial study designed with both intervention and control arms. The study will involve 268 children with a viral load of >1000 copies/ml who are aged between 2 and 14 years. The children will be randomly allocated into the intervention and control arms. The intervention will include three distinct activities: adherence and retention counseling, psychosocial support, and comorbidity screening (i.e. tuberculosis). The outcome of the study will be assessment of the success of the intervention to increase medication adherence with the immediate result of reducing the viral load below 1000 copies/ml. Descriptive statistics will be used to calculate the mean, median, standard deviation, and interquartile range of continuous data. We will use frequencies and percentages to summarize categorical data. As for the primary outcome (proportion of HIV-infected children with viral suppression), we will compare the proportion of successful participants in the intervention and control arms. Proportions and tests for different proportions will be used as a measure of improvement. All statistical tests will be two-sided and *P* < 0.05 will be considered statistically significant.

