### Intervention

The UNAIDS and previous studies have recommended the engagement of communities, from small informal groups at the grassroots level up to global coalitions, to improve HIV care [31]. The National Council of PLHIV (NACOPHA) is a non-profit, non-government organization. It is a national grassroots-based organization of all individuals who are recognized through organized groups and clusters of PLHIV in Tanzania mainland. Since its establishment has embarked upon coordinating the efforts of PLHIV through their district clusters known as “Konga” to address the needs of PLHIV. Konga is a Swahili name meaning that is a Cluster of PLHIV at the district level, thus Konga is the smallest unit of NACOPHA. Hence, we will use the community of PLHIV known as Konga to provide services to children.

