#### Roles of the Konga

We will provide the standard operating procedures (SOPs) to the Kong such that different person will use for the provision of the desired intervention. The SOP will have specific standards adapted from the National HIV care and treatment guidelines, thus the Konga will use the SOP:

To provide enhanced adherence counseling and intensive follow-up. Here, the Konga will routinely visit the client’s house and at every visit they will assess and document:∘ Medication regimen, storage of drugs at home.∘ Doses missed: how often, why, then solve problem with the client.∘ Side effects such as headache, nausea and vomiting, diarrhea, fatigue, sleeping, difficulty, a dry mouth, a rash, dizziness and a pain and client response.∘ Use of other medications, including traditional medicines.∘ Challenges.Follow-up screening for TB and other comorbidities (members of the Konga will visit the children and screen for opportunistic infection and encourage them to visit the health facility for further management); andProvision of psychosocial support by members of the Konga team.

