### Sample size calculation and selection

The trial will be conducted in 20 CTC clinics that deliver HIV care and treatment within the four selected districts (10 CTCs will carry out the intervention and 10 CTCs will carry out standard care). We determined the study size from the primary outcome of proportional HIV-positive children with a viral load >1000 copies/ml. According to THIS (2018), 18% of HIV-positive children under the age of 15 years had a viral load >1000 copies/ml; thus, we assumed that value for standard care. Therefore, under a cluster design, the study will need a total sample size of about 268 children (134 in the intervention group and 134 in the control group) to increase the proportion of children with viral suppression from 18% to 30% with 80% power, ata5% significance level, an intra-cluster correlation of 0.01, and 10% expected loss to follow-up. We carried out this power calculation using the Stata™ function “clustersampsi” command (clustersampsi, binomial p1[0.18] p2[0.3]k[20] rho[0.01] alpha[0.05] beta[0.8]).

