### Selection and randomization of CTC

A site assessment will be performed before the final site selection and sites will be selected to participate in the study based on infrastructure feasibility, last numbers of children enrolled into CTC during the past year, numbers and qualification of staff affiliated to CTC and balanced representation of the different level of health facilities and urban versus rural affiliations. Assignment of sites to one of the two study arms will be done by randomization (Fig. 1). Stratification during the randomization process (e.g. rural versus urban) will be considered.

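### The article contradicts itself on whether control children receive Konga screening visits, and district-level Kongas will almost certainly work in districts that hold both arms

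*Protocol article*

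**What the plan says.** On the control condition, *Sample size calculation and selection* sets the comparison: "10 CTCs will carry out the intervention and 10 CTCs will carry out standard care". The *Abstract* names comorbidity (tuberculosis) screening as one of three intervention activities, beside adherence counselling and psychosocial support. *Roles of the Konga* assigns that screening to visits: "members of the Konga will visit the children and screen for opportunistic infection". The *Discussion* then states: "The Konga model will include active home visits to screen children for TB and other co-morbidities in the control arm".

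On delivery and allocation, *Intervention* describes the Konga as "a Cluster of PLHIV at the district level" and as the smallest unit of its parent organisation. *Role of the health worker* has ART nurses at the selected facility link eligible children to the Konga, without naming an arm. The 20 CTCs lie in four districts and are randomised as sites. On strata, *Selection and randomization of CTC* says only: "Stratification during the randomization process (e.g. rural versus urban) will be considered". *Follow-up data* covers adherence, retention and opportunistic infections monthly in both arms. Contact with the Konga is not among the items listed.

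**The concern.** The comparator fixes what the trial estimates. If control children receive Konga screening visits, the comparison is no longer the full Konga package against standard care. It becomes the package against care that already contains one of its three components, and a smaller difference would be expected if that component works.

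The second matter is a mismatch of units. Treatment is delivered by a district body but allocated by clinic. Where one district holds clinics of both arms, the same Konga works in the catchments of both, and the article does not say how its visits are kept to intervention children. If control children are visited, the estimate is drawn towards no difference. With no record of Konga contact, a null result could not be told apart from contamination.

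**Working it through.** **1. The control condition, section by section**

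- *Abstract*: screening is an intervention activity.
- *Roles of the Konga*: screening is done by Konga visit; no arm is named.
- *Sample size calculation and selection*: control CTCs give standard care.
- *Discussion*: Konga screening visits take place in the control arm.

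The last statement cannot hold together with the first and third. *Role of the health worker* does not settle it, because it names no arm. Nor does *Follow-up data*, which has opportunistic infections observed in both arms without saying by whom.

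**2. Will a Konga work in a district that holds both arms?**

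Inputs: 20 CTCs, 10 per arm, four districts (all from the article). Assumptions: one Konga per district and unrestricted 10/10 allocation.

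- Possible allocations: C(20,10) = 184,756.
- No district is shared only if the intervention arm is made up of whole districts totalling 10 CTCs. With five CTCs in each district (not stated in the article), this means choosing two districts of four: C(4,2) = 6 allocations.
- Chance of no shared district: 6/184,756 = 0.003%.
- The bound does not depend on five per district. Two sets of districts with the same total cannot be nested, and four items yield at most six such sets. Six is therefore the maximum for any division of the 20 CTCs among four districts.

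**3. District imbalance between arms** (assuming five CTCs per district and unrestricted allocation)

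- Every district split 3-2 or 2-3: 6 × 10⁴ = 60,000 allocations. Chance of at least one split of 4-1 or worse: 1 − 60,000/184,756 = 67.5%.
- Every district with at least one CTC in each arm: 163,750 allocations. Chance that at least one district falls wholly in one arm: 1 − 163,750/184,756 = 11.4%.

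**4. What dilution would do, as a hypothetical**

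The plan's own figure first. For 18% against 30%, 80% power and two-sided 5%, the individually randomised size is (1.96 + 0.8416)² × (0.1476 + 0.21)/0.12² = 195 per arm. With intra-cluster correlation 0.01 and 10 CTCs per arm, m = 194.9 × 0.99/(10 − 1.949) = 23.97. That rounds to 24 per CTC, or 240 per arm, and 240/0.9 = 267 per arm. The stated 268 thus matches one arm, not the total. This is a separate matter; it is noted only because it explains why the starting power below is not 80%.

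At 134 per arm, 134 × 0.9 = 120.6 are evaluable, and the design effect is 1 + (12.06 − 1) × 0.01 = 1.111. Let c be the average share of the 12-point effect that reaches controls, so that the control rate is p = 0.18 + 0.12c. Then SE = √{[p(1 − p) + 0.21] × 1.111/120.6} and power = Φ((0.30 − p)/SE − 1.96).

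| c | control rate | SE | power |
|---|---|---|---|
| 0 | 0.18 | 0.0574 | 55% |
| 1/12 | 0.19 | 0.0579 | 48% |
| 1/4 | 0.21 | 0.0588 | 33% |
| 1/3 | 0.22 | 0.0593 | 27% |
| 1/2 | 0.24 | 0.0601 | 17% |

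The article gives no value of c. As an illustration, c = 1/3 would arise if every control child were screened and screening carried a third of the effect; c = 1/12 would arise if a quarter of them were. The table shows only how wide the range is.

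**The case against.** The *Discussion* sentence describes the Konga model, and a single wrong word may account for it. The Methods do state a comparison, with ten intervention and ten standard-care CTCs. A reader might infer that the contrast is undefined. That goes too far, because the article defines it and then contradicts it once. The contradiction still concerns the comparator and needs resolving.

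A reader might also infer that sharing a Konga means control children will be visited. The article does not say so. A child reaches the Konga through a nurse's referral, so a control child who is never linked need not be visited. How members are kept to intervention children is also detail that an article may leave to the full protocol. This objection stands in part: contamination is a risk inferred from the design. It is not excluded, because the referral text names no arm.

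A third tempting inference is that district imbalance would make a difference unattributable to the intervention. It would not. A 4-1 split in one district is chance imbalance under randomisation, and the other districts can still hold both arms. Complete confounding of arm with district has the same chance of about 0.003%. Nor does the rural/urban example rule out district as a stratum.

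Finally, balancing arms within every district guarantees the shared Kongas that create the contamination risk. That is correct, and the remedy has to admit it.

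**Conclusion.** The point stands in two parts of unequal certainty.

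The contradiction over control-arm screening is plain from the text and must be reconciled. The documents do not settle which statement is meant, and none is preferred here.

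The overlap of arms within a Konga's district is close to certain (at least 99.99% under unrestricted 10/10 allocation with one Konga per district), and it would remain after the wording is corrected. Whether overlap becomes contamination, and how much, cannot be computed from the article. The powers of 17% to 48% rest on assumed dilution shares and are not findings. The 67.5% and 11.4% imbalance figures rest on an assumed five CTCs per district and say nothing about the size of any bias. They support using district in the analysis but do not show that the result would be uninterpretable.

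**What to change.** 1. Reconcile the *Discussion* with the *Abstract*, *Roles of the Konga* and *Sample size calculation and selection* on what control children receive.
2. In *Role of the health worker*, state which arm's children are linked to the Konga.
3. Add Konga contact (yes/no) to the monthly follow-up in both arms, and report it by arm. This measures contamination; it does not prevent it.
4. Include district as a factor in the regression that already adjusts for clustering. If allocation has not been done, use district as a randomisation stratum as well.

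The cost is some wording, one question on an existing form and, if still possible, an allocation list stratified by district. Four districts use three degrees of freedom; at cluster level 20 − 2 = 18 becomes 15. The stratum has a real downside: it places both arms under every Konga. It therefore addresses district imbalance and not contamination, which is why item 3 is needed alongside it.
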